**Stool metagenomics:** Faecal samples in cryotubes are removed from the -80°C freezer, allowed to defrost and 30mg is used for DNA extraction. The FastDNA Spin Kit for Soil also incorporates a bead beating step to lyse bacterial cells which is performed using the FastPrep-24™ Classic bead beating grinder and lysis system (also supplied by MP Biomedicals). Negative controls using sterile Phosphate-buffered saline (PBS) are included for each extraction batch (24 samples per extraction batch). Total DNA is eluted in DNase/Pyrogen-free water and stored at -80°C until metagenomic sequencing. DNA samples, including negative controls, are quantified and subjected to paired-end (2 x 151bp) metagenomic sequencing on the NovaSeq (Illumina, USA) S4 XP with 192 samples per flow cell (targeting 13 million reads or 4 Gb / sample). Low-quality bases are trimmed using Trim Galore v0.5.0 with default parameters. Potential human contaminant sequences are removed by screening against the human genome (GRCh38) with BMTagger v1.1.0. Quality-controlled, paired-end reads will be independently assembled with metaSPAdes23 v3.13.0 using default parameters. Taxonomic classification from metagenomics reads will be performed using a reference genome mapping approach using the Human Gastrointestinal Bacteria Genome Collection enriched with Metagenome Assembled Genomes (MAGs) generated from the study metagenomes
^
71
^.

**Faecal pathogen detection:** Total nucleic acid will be extracted from rectal swab and tested using the enteric TaqMan Array Card (TAC, Life Technologies, USA) developed by the Houpt Lab at The University of Virginia
^
66
^. The custom enteric TAC targets multiple pathogens simultaneously including bacteria, viruses, helminths, and protozoa. The card is a 384-well microfluidic real-time PCR format for TAC-compatible instrument platforms. Briefly, both DNA and RNA are extracted from faecal swab specimens using the QIAamp Fast DNA Stool MiniKit (Qiagen, Germany) as previously described
^
72
^. The faecal sample undergo a lysate preparation process that includes mechanical disruption (bead beating), removal of inhibitors, purification and elution of DNA and RNA using spin columns. The extracted total nucleic acid is then used for testing. 40 µL of total nucleic acid extract is mixed with 50 µL of AgPath One Step RT-PCR buffer and 4 µL of enzyme mix (Life Technologies) in a 100 µL reaction, then loaded onto the microfluidic card by centrifugation at 1,200 rpm, 1 min for twice, followed by sealing and cutting off the loading ports. The cards are analysed in a ViiA7 or QuantStudio 7 Flex instrument (Life Technologies, USA). The cycling conditions are set as follows: 45°C for 20 minutes and 95°C for 10 minutes, followed by 40 cycles of 95°C for 15 s and 60°C for 1 minute. Extrinsic controls (MS2 bacteriophage and Phocine herpesvirus) are added to each sample during the lysate preparation to evaluate extraction and amplification efficiency while blank controls help rule out contamination during the extraction process. The assay uses predefined thresholds although the baseline for each target may require adjustment. A sample is deemed positive for a particular target when an appropriately shaped amplification curve crosses the analytical threshold for positivity before or at cycle 34.9 and negative if the curve does not cross the threshold line or crosses the threshold line at cycle 35.0 or later. Pathogen quantities in copy number are derived based on the standard curve for each target.

**Faecal biomarkers of enteropathy: Stool** myeloperoxidase, alpha-1-antitrypsin, and calprotectin will be quantified using the ELISA assay (Immundiagnostik AG, Germany) according to manufacturer’s instructions. The absolute concentration of the three biomarkers in samples will be calculated for 15 mg of stool using a dose response curve generated from the manufacturer’s standards.

**Haemoglobin variants:** Ion-exchange high-performance liquid chromatography (HPLC) will be used for separation and quantification of HB variants in dry blood spots (DBS) using the D-10 Haemoglobin Testing System (Bio-Rad, USA). DBS are resuspended on a lysis buffer to release haemoglobin. The samples are then diluted on the D-10 Haemoglobin Testing System (Bio-Rad, USA) and injected into the analytical cartridge. The D-10 delivers a programmed buffer gradient of increasing ionic strength to the cartridge, where the haemoglobin variants are separated based on their ionic interactions with the cartridge material. The separated haemoglobin then pass through the flow cell of the filter photometer, where changes in the absorbance at 415 nm are measured. The D-10 System will be used for quantitation of haemoglobins variants namely: A, S, F and A2 and other minor variants and diagnosis of ß-thalassaemia and sickle cell anaemia among study children.

**Serum aflatoxin:** The analysis of aflatoxin-albumin (AF-alb) will follow the method first described by Chapot and Wild
^
73
^ and detailed by Xu and colleagues
^
67
^. In brief, albumin is extracted from serum samples, hydrolysed overnight using pronase and purified with Sep-pak C-18 cartridges (Waters, MO, USA). AF-alb is quantified using a competitive ELISA
^
67
^ with a limit of detection (LOD) of 3pg AF-lysine equivalents per mg albumin. Each ELISA includes positive and negative control samples for quality control. All samples are measured in duplicate for each ELISA batch and repeated at least two times on separate days to confirm the results. Results are accepted when values within each ELISA have a %CV below 10% and samples tested on separate occasions had a %CV below 15%. Samples with concentrations above the linear range of the standard curve are repeated at a suitable dilution. This ELISA has been validated for measuring aflatoxin albumin biomarker levels against dietary aflatoxin intake
^
68,
69
^, and also against an LC-MS assay for measuring aflatoxin lysine
^
74
^. Whilst the ELISA consistently gives Af-alb values that are approximately three-fold higher than aflatoxin lysine values, the results between these methods correlate for the same samples. The AF-alb values are, therefore, suitable for use in analyses to compare variations in aflatoxin exposure in relation to health outcomes or other variables such as child growth.

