### Study design

A nested case-cohort design drawing from a larger cohort provides estimates that are representative of the entire cohort while also yielding slightly more statistical power than a case control design
^
58
^. Case-cohort selection involves a random subsample of the original cohort (sub-cohort), independently of how cases are defined, followed by additional inclusion of all cases outside the sub-cohort creating the case-cohort set
^
59
^. This results in overrepresentation of the cases in the case-cohort set compared to the original cohort which is dealt with in analysis by weighting. A further advantage of this design over a case-control design is that the sub-cohort can also be used in analysis of other outcomes. In CHAIN, this could include outcomes of readmission or growth among survivors in future analyses, as well comparisons between acutely ill children and community children and between nutritional strata among acutely ill children in the current analysis.

The original CHAIN cohort stratification was maintained in the CNCC design; thus, a random 24% sub-cohort of children enrolled in the CHAIN cohort stratified by site was selected. This included 658 survivors (sub-cohort non-cases) and 109 deaths (sub-cohort cases). Thereafter, all remaining deaths (n=241 cases) that were not selected in the random 24% sub-cohort (
Figure 3) were added, giving a total of 350 cases. An additional 30 randomly selected community participants from each site (total N=270) were chosen.

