Full chromatographic separation of intact lipids is achieved using Waters Acquite H-class UPLC System (Waters, Hertfordshire, United Kingdom) with the injection of 10 µL onto a Waters Acquity UPLC® CSH C18 column (Waters, Hertfordshire, United Kingdom); 1.7 µm, I.D. 2.1 mm × 50 mm, maintained at 55°C. Mobile phase A is 6:4, acetonitrile and water with 10 mM ammonium formate. Mobile phase B is 9:1, propan-2-ol and acetonitrile with 10 mM ammonium formate. The flow is maintained at 500 µL per minute through the following gradient: 0.00 minutes_40% mobile phase B; 0.40 minutes_43% mobile phase B; 0.45 minutes_50% mobile phase B; 2.40 minutes_54% mobile phase B; 2.45 minutes_70% mobile phase B; 7.00 minutes_99% mobile phase B; 8.00 minutes_99% mobile phase B; 8.3 minutes_40% mobile phase B; 10 minutes_40% mobile phase B. The sample injection needle is washed using 9:1, 2-propan-2-ol and acetonitrile. The Thermo Scientific Exactive Orbitrap mass spectrometer with a heated electrospray ionization source (Thermo Fisher Scientific, Hemel Hempstead, UK) is used. The mass spectrometer is calibrated immediately before sample analysis using positive and negative ionization calibration solution (recommended by Thermo Scientific). Additionally, the mass spectrometer scan rate is set at 4 Hz, giving a resolution of 25,000 (at 200 m/z) with a full-scan range of m/z 100 to 1,800 with continuous switching between positive and negative mode.

The instrument responses of the analytes, selection based on retention time and accurate
*m/z*, are normalized to the relevant internal standard response (producing area ratios). These area ratios correct the intensity for any extraction and instrument variations. The area ratios are then blank corrected where intensities less than three times the blank samples are set to a ‘Not Found’ result (i.e., zero concentration). The accepted area ratios are then multiplied by the concentration of the internal standard to give the analyte semi-quantitative concentrations.

**Plasma lipopolysaccharides:** Endotoxin levels in EDTA plasma samples are measured via a Limulus Amoebocyte lysate-based, quantitative chromogenic endpoint assay (ThermoFisher, UK). The assay is performed based on a protocol described previously
^
65
^. Briefly, 50 µL of plasma is diluted 1:3 in 100 µL 10 mM MgCl

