### Statistical analysis

**
*Descriptive analysis.*
** The distribution and prevalence of biomarkers in laboratory assays which have clear clinical interpretations will be described at admission and discharge timepoints across the nutritional strata and compared with community participants. These more targeted assays will include the serum micronutrients, serum aflatoxin biomakers, plasma lipopolysaccharides, haemoglobin variants, faecal biomarkers of enteropathy, and faecal pathogens. For these assays, the crude and confounder adjusted case fatality rates, which will be appropriately weighted for selection into the NCC analysis and the original CHAIN cohort, will be described.

The appropriate non-parametric statistical test will be employed to calculate the significance of the association between each feature and each outcome or measure of interest in every relevant subset of patients. For binary outcomes (i.e., the primary outcome of mortality), the Wilcoxon rank sum test will be used to determine the significance of the association while Hedge’s g will be used to calculate the effect size of the difference between groups. For continuous measures, the Spearman’s rank correlation coefficient will be used to assess the strength and significance of the association between the feature and the measure. Linear regression models will be fit for each feature against the confounding variables of interest and the residuals taken as the confounder-adjusted features.

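### Rank-testing linear-regression residuals of lipids whose non-detects are coded zero orders those non-detects by the confounder, and can create false associations with death when non-detects are common

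*Protocol article*

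**What the plan says.** Three stated rules combine.

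- **Non-detects** (Detailed methods, Serum lipidomics): "intensities less than three times the blank samples are set to a ‘Not Found’ result (i.e., zero concentration". Values that pass are put on a concentration scale: "The accepted area ratios are then multiplied by the concentration of the internal standard to give the analyte semi-quantitative concentrations". No transformation for lipids is stated or ruled out.
- **Adjustment** (Statistical analysis, Descriptive analysis): "Linear regression models will be fit for each feature against the confounding variables of interest and the residuals taken as the confounder-adjusted features".
- **Test** (same paragraph): for mortality, "the Wilcoxon rank sum test will be used to determine the significance of the association". The scope is the "significance of the association between each feature and each outcome or measure of interest", which by its wording includes lipids.

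The group sizes are in Study design: "This included 658 survivors (sub-cohort non-cases) and 109 deaths (sub-cohort cases" and, with the remaining deaths added, "giving a total of 350 cases".

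The article gives no share of non-detects, no detection-frequency filter for lipids and no list of confounders.

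**The concern.** A rank test copes well with non-detects as long as they remain tied. The residual step breaks the ties, and does so with the confounder and nothing else. If the confounder differs between deaths and survivors, the adjusted test can then report a lipid as associated with death when it is not, and when the crude test shows nothing.

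The Introduction says that lower nutritional status, signs of illness severity and HIV were associated with mortality in this cohort, so a death-related confounder is plausible. At stake are false lipid signals in a study whose purpose is mechanistic insight to guide interventions.

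**Working it through.** **Counts.** 109 + 241 = 350 deaths. With 658 survivors, n = 1,008. Adding 270 community children gives 1,278, as stated.

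**Mechanism.** With feature x, confounder C and fitted line a + bC, the residual is r = x − (a + bC). For a non-detect x = 0, so r = −(a + bC). Among non-detects, the order of r is therefore exactly the order of C, forwards or reversed by the sign of b. The size of b does not matter: a slope that is pure noise orders the ties just as completely. In simulation the absolute Spearman correlation between r and C among non-detects was 1.000, including when the lipid was unrelated to C. With several confounders, the fitted score takes the place of C.

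**Assumptions (not in the documents).** One normal confounder, shifted by d SD in deaths; a log-normal lipid with correlation ρ to C on the log scale and no link to death given C; the lowest fraction p coded zero; two-sided 5%; no case-cohort weights.

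**Hand check, ρ = 0.** Of all death–survivor pairs, a share p² are both non-detects and are now ordered by C. The expected shift of the Wilcoxon z is about

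p² × n₁n₀ × [Φ(d/√2) − 0.5] / √(n₁n₀(n + 1)/12).

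Here n₁n₀ = 350 × 658 = 230,300, and the denominator is √(230,300 × 1,009/12) = 4,400.5. For d = 0.6, Φ(0.424) − 0.5 = 0.1643, so the shift is 8.60p². For d = 0.3 it is 4.40p². For example, d = 0.6 and p = 0.6 give 3.10, and P(|Z + 3.10| > 1.96) = 87%.

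**Simulation, ρ = 0, 2,000 runs per cell, rejection at nominal 5%.**

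| d | Non-detects | Hand check | Zero-coded residual | Uncensored raw residual | Log half-limit residual |
|---|---|---|---|---|---|
| 0.3 | 20% | 5% | 6.2% | 6.0% | 5.4% |
| 0.3 | 40% | 11% | 11.6% | 5.3% | 9.8% |
| 0.3 | 60% | 35% | 34.0% | 5.5% | 32.8% |
| 0.3 | 80% | 80% | 77.9% | 5.2% | 77.2% |
| 0.6 | 20% | 6% | 8.7% | 7.7% | 4.7% |
| 0.6 | 40% | 28% | 27.5% | 8.4% | 23.5% |
| 0.6 | 60% | 87% | 87.9% | 8.0% | 86.8% |
| 0.6 | 80% | >99% | about 100% | 8.0% | about 100% |

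A separate set of 1,500 runs per cell gave the same picture. In that set the crude Wilcoxon test on zero-coded values, with ties kept, rejected in 3.7% to 5.5%. With d = 0 there was no inflation (4.2% at 60% non-detects).

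**After Bonferroni.** With 500 tests assumed (threshold 0.0001), d = 0.6 and ρ = 0, a null lipid is still declared significant in 19% of runs at 60% non-detects and 94% at 80%. The hand formula gives 21% and 95%.

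**Correlated lipid, ρ = 0.3, d = 0.6.** The uncensored raw-scale residual already rejects in 41% to 43%. Zero coding gives 31%, 44% and 98% at 20%, 60% and 80% non-detects. The zeros lower the rate at 20%, barely change it at 60% and raise it sharply at 80%.

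**Joint adjustment.** Regressing the ranks (zeros tied) on death and C in one model gave 4.1% to 6.2% in every cell tested.

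**The case against.** The strongest reply is that the size rests on inputs the article does not give: the share of non-detects, the confounder gap and the lipid–confounder correlation. A full plan may apply a transformation or a detection filter, and a condensed article may properly leave both to it. That stands as a limit on size. A strict detection filter would remove the worst-affected lipids. A log transform with a substituted value would not, as the half-limit column shows.

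Four stronger readings are tempting and are not supported:

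- **That the regression is on the raw scale.** The scale is not stated, and the mechanism does not need it.
- **That the zeros explain most of any inflation.** Where lipid and confounder are correlated, much of the inflation on an untransformed scale comes from skew under a linear fit. At moderate non-detect shares, zero coding mostly lowered rejection against the uncensored lipid.
- **That pathway results inherit the fault.** The Pathway enrichment analysis section covers genes and proteins, so lipids do not enter it. Nor does the article say that the residuals feed the predictive models.
- **That coding zero is itself the error.** Kept as ties in a joint model, or in the crude test of a lipid unrelated to the confounder, the zeros do no harm.

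One could also say that the article never states in one sentence that the Wilcoxon test is run on the residuals. But residuals called confounder-adjusted features, in the paragraph that names the test, have no other evident use.

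**Conclusion.** The point holds in conditional form. The zero rule, the residual step and the rank test are all stated, and together they rank non-detects by the confounder score. That part is algebra.

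False associations with death can follow when the confounder is related to death and non-detects are common, roughly 40% or more. For a lipid unrelated to the confounder and a 0.6 SD gap, rejection at nominal 5% is about 28%, 87% and over 99% at 40%, 60% and 80% non-detects. For a 0.3 SD gap it is about 12%, 34% and 78%. At 20% or fewer non-detects, or with a confounder unrelated to death, the zeros add essentially nothing. Bonferroni correction does not protect at the higher shares.

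The seat of the problem is the adjustment method in Statistical analysis, not the laboratory rule. The change should be made, because it is cheap and the adjusted test cannot be trusted for heavily censored lipids.

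**What to change.** In Statistical analysis, Descriptive analysis, state that features with non-detects are not rank-tested on regression residuals. Adjust for the confounders jointly with death in one model, with the case-cohort weights. Either form will do:

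- an outcome model for death with the confounders, a detected yes/no term and the log level among detected; or
- a rank or ordinal model of the feature on death plus the confounders, with non-detects kept as ties.

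In unweighted simulation the first form rejected in about 3% to 8% of runs and the second in 4.1% to 6.2%. In Serum lipidomics, keep 'Not Found' results flagged as below the limit, so that they can be told apart from a measured value. State the analysis scale and any detection filter where the adjustment is defined.

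The cost is analysis wording and code, and at most one extra degree of freedom per lipid. No samples or assays change.

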### Statistical analysis

**
*Descriptive analysis.*
** The distribution and prevalence of biomarkers in laboratory assays which have clear clinical interpretations will be described at admission and discharge timepoints across the nutritional strata and compared with community participants. These more targeted assays will include the serum micronutrients, serum aflatoxin biomakers, plasma lipopolysaccharides, haemoglobin variants, faecal biomarkers of enteropathy, and faecal pathogens. For these assays, the crude and confounder adjusted case fatality rates, which will be appropriately weighted for selection into the NCC analysis and the original CHAIN cohort, will be described.

The appropriate non-parametric statistical test will be employed to calculate the significance of the association between each feature and each outcome or measure of interest in every relevant subset of patients. For binary outcomes (i.e., the primary outcome of mortality), the Wilcoxon rank sum test will be used to determine the significance of the association while Hedge’s g will be used to calculate the effect size of the difference between groups. For continuous measures, the Spearman’s rank correlation coefficient will be used to assess the strength and significance of the association between the feature and the measure. Linear regression models will be fit for each feature against the confounding variables of interest and the residuals taken as the confounder-adjusted features.

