### Sample size

Multiple studies in both low- and high-income settings indicate a prolonged increased mortality risk after admission (including >1 year) compared to the community peers
^
10,
43,
60
^ which is now considered a well-recognised phenomenon. The primary analyses will be of acute mortality occurring within 30-days from admission and post-discharge mortality within 180-days from discharge using samples collected at admission and discharge timepoints. Power and effect size are a function of the number of cases, correlation between cases and survivors, and the ratio of cases to survivors. It is likely that the strength of association between exposures of interests and death will vary in magnitude between the 30-day and 180-day mortality periods. Sample size calculations suggest that a ratio of one case to two non-cases is adequate to reliably detect an HR of 1.5 at >80% power. The design selected all available deaths and simulation-based power calculations suggested that adding more non-cases per cases would yield minimal gains in power while incurring substantial additional expense.

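### The test named for primary mortality yields no hazard ratio and has no stated use of case-cohort weights or site strata, although the study was sized on HR 1.5 and weighting is promised

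*Protocol article*

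**What the plan says.** All references are to the protocol article.

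- **Sample size.** Two time-defined endpoints are named: "The primary analyses will be of acute mortality occurring within 30-days from admission and post-discharge mortality within 180-days from discharge". The sizing statement is that "a ratio of one case to two non-cases is adequate to reliably detect an HR of 1.5 at >80% power".
- **Study design.** A sub-cohort of about 24%, stratified by site, was drawn, and all remaining deaths were added. The resulting over-representation of cases is something "which is dealt with in analysis by weighting".
- **Statistical analysis, Descriptive analysis.** The text reads "For binary outcomes (i.e., the primary outcome of mortality" and goes on to say that "the Wilcoxon rank sum test will be used to determine the significance of the association". Hedges' g "will be used to calculate the effect size of the difference between groups". Features are also to be regressed on confounders and the residuals used as adjusted features, but the confounders are not listed. Weights are mentioned once in this section, for the case fatality rates of the targeted assays.
- **Elsewhere.** No Cox model or other time-to-event model appears in the analysis sections.

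**The concern.** Three sections describe three different analyses. The design section implies a weighted case-cohort analysis, the sizing section a hazard-ratio analysis, and the analysis section a two-group rank test with a standardised mean difference. A standard rank sum test and Hedges' g use neither sampling weights nor follow-up time, and they produce no hazard ratio. The planned HR of 1.5 therefore cannot be set against any planned estimate.

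The choice has a numerical consequence for 30-day death. A child who dies after day 30 is a non-case for that endpoint. All such children were selected, whereas only about a quarter of survivors were. A two-group comparison has to include the late deaths unweighted, which over-represents them, or drop them, which conditions on surviving all later follow-up. The article does not say which.

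**Working it through.** **1. Counts (Study design; Participant enrolment).**
- Sub-cohort: 658 + 109 = 767, and 767/3101 = 24.7%.
- Cases: 109 + 241 = 350.
- Survivors in the full cohort: 3101 - 350 = 2751. Sampled: 658/2751 = 23.9%, a weight of 2751/658 = 4.18.
- Deaths: all sampled, weight 1.
- Non-cases per case: 658/350 = 1.88, close to the stated two.

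**2. The plan's own power figure.** Alpha, exposure prevalence and the number of cases per endpoint are not given, so the figure of more than 80% cannot be strictly reproduced. At two-sided 0.05 with HR 1.5 and exposure prevalence p:
- Schoenfeld formula, power = Φ(√(D·p(1-p))·ln 1.5 - 1.96), with D = 350: 96.7%, 93.5% and 85.9% at p = 50%, 30% and 20%.
- Case-cohort log-rank formula, with q = 767/3101 and d = D/3101: power = Φ(√767·ln 1.5·√(p(1-p)d/(q+(1-q)d)) - 1.96). For D = 350 this gives 90.5%, 85.1%, 74.5% and 50.1% at p = 50%, 30%, 20% and 10%. For an assumed D = 175 per endpoint it gives 69.8%, 62.2%, 50.9% and 31.8%.
- For a continuous feature with HR 1.5 per SD, approximated as a mean shift of ln 1.5 = 0.405 SD, power is about 99% or more even with 175 cases, including for the rank test.

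The stated figure is therefore plausible for a hazard analysis of all deaths. None of the hazard-based figures is the power of a test reported with Hedges' g. No power loss from using the rank test is shown.

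**3. The 30-day contrast.** The Introduction says about half of mortality follows discharge. The split at day 30 is not given, so I assume 175 early and 175 late deaths. I also assume both are shifted by 0.6 SD from survivors.
- Late deaths as a share of non-cases: in the cohort 175/(175 + 2751) = 175/2926 = 6.0%; unweighted in the sample 175/(175 + 658) = 175/833 = 21.0%.
- Cohort contrast: 0.6 × (1 - 175/2926) = 0.564 SD.
- Late deaths included unweighted: 0.6 × (1 - 175/833) = 0.474 SD, and 0.474/0.564 = 0.84 (-16%).
- Late deaths dropped: 0.60 SD, and 0.60/0.564 = 1.06 (+6%).

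The relative error does not depend on the size of a common shift: at 0.405 SD the contrasts are 0.320 and 0.381, again -16%. It does depend on the number of late deaths L, through [658/(658+L)]/[2751/(2751+L)]. As an illustrative range, L = 100 gives 0.868/0.965 = 0.90 (-10%) and L = 250 gives 0.725/0.917 = 0.79 (-21%). If late deaths looked like survivors at admission, there would be no distortion either way.

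**4. Does over-sampling deaths alone distort the test?** For ever-died against never-died, the case-cohort weights are nearly constant within each group (1 and about 4.2). In simulation (9 sites, 24% sub-cohort, all deaths added, 1,000 runs per setting, no site differences in the feature), the rank test rejected a true null in 3.6% to 5.1% of runs. So it does not.

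**5. Site.** With no within-site effect, an assumed between-site feature SD of 0.5 and log mortality spread of ±0.4 to ±0.8, rejection at nominal 5% was:

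| Test | ±0.4 | ±0.8 |
|---|---|---|
| Rank sum, raw feature | 9.8% | 22.4% |
| Site-stratified (van Elteren) | 5.5% | 5.3% |
| Rank sum, site-residualised feature | 5.3% | 3.9% |

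Inflation arises only if site is left out of the residual step.

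**The case against.** The strongest reply is that this is a condensed article with an analysis plan not shown. A reader might infer that the mortality test is definitely unweighted and ignores site. The text says neither. It is silent on both, and the general statement on weighting in the Study design section could be read as covering every analysis. That stands, so the point is limited to what is fixed in print: a named test and effect measure that do not fit the sizing or the design.

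A reader might also infer that site differences will produce false associations. The documents do not support that as a prediction. Residual adjustment is planned, site is among the recorded characteristics, and adjusting for it returns the error rate to about 5%. Nor does over-sampling deaths by itself invalidate a died versus never-died rank test (step 4).

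The two endpoints have different time origins, so an early-discharged child who dies before day 30 counts in both, and an in-hospital death after day 30 counts in neither. That is a property of the endpoints. A Cox model would leave it unchanged, so it is no argument against the rank test.

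Finally, the test sits under a descriptive subheading and works as a per-feature screen. This is fair, but the same sentence assigns it the significance testing of the primary outcome, and no other inferential analysis of a single feature against mortality is described.

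**Conclusion.** The concern holds in this form. The test and effect measure stated for primary mortality do not deliver the hazard ratio on which the study was sized, and the promised weighting is carried explicitly only to case fatality rates. The Study design, Sample size and Statistical analysis sections need to be reconciled.

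The measurable consequence is confined to 30-day death: 0.47 SD with late deaths included unweighted, or 0.60 SD with them dropped, against 0.56 SD in the cohort. This rests on an assumed 175/175 split and an equal 0.6 SD shift in early and late deaths. The first error is towards the null and the second is small. For the 180-day endpoint the case-cohort weights are nearly constant within group, so this problem does not arise. Any weights for the cohort's own enrolment by arm-circumference strata, which the article mentions for case fatality rates, could still vary within groups. Site confounding is a conditional risk that the article leaves open by not listing the adjustment covariates.

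**What to change.** For each mortality endpoint, make the inferential analysis a case-cohort weighted Cox model with robust variance, stratified by site, with confounders in the same model.

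- **30-day death:** admission samples, time from admission, censored at day 30. Later deaths stay in as non-cases with their correct weight, and survivors are weighted by the inverse of their sampling fraction.
- **Post-discharge death:** discharge samples in children discharged alive, time from discharge, censored at day 180.
- **Feature scale:** chosen to suit the feature, for example per SD of a transformed continuous feature, or present/absent for pathogen calls and features with many zeros.
- **Wilcoxon and Hedges' g:** kept as descriptive or screening results, on features residualised for site, and labelled as such.

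This needs a change of wording, standard software and data already held, with no new samples. The downside is small: more analysis work, and a proportional-hazards check that can be limited to the top features rather than run on some 7000 proteins. The choice should be settled before results are examined.
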